## **Study Drugs**

- **Hydroxychloroquine:**

400mg bid for first day then 200mg bid for 10 days

- **lopinavir/ritonavir (Kaletra):**

400mg/100mg bid for 10-14 days

For those that could not get orally:

5-ml suspension bid for 10-14 days

- **Interferon beta-1a:**

SC injection 44 micro-gram for 3 days (on days 1,3,6)

- **Interferon beta-1b:**

SC injection 0.25 mg for 3 days (on days 1,3,6)

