**Participants:**

Sixty COVID-19 confirmed cases (using the RT-PCR test) will be enrolled in the trial between April 9^th^ to April 14^th^ 2020. Patients will be randomly assigned to the intervention groups or the control group with the following eligibility criteria: ≥ 18 years of age AND (oxygen saturation (SPO2) ≤ 93% OR respiratory rate ≥ 24) AND at least one of the following: Contactless infrared forehead thermometer temperature of ≥37.8°C, cough, sore throat, nasal congestion/drip, myalgia, headache or fatigue on admission, and onset of the symptoms should be acute (Days ≤ 14). Although Hydroxychloroquine will be administered in a single dose, patients with heart problems (prolonged corrected QT (450 milliseconds) or PR intervals, second- or third-degree heart block, and history of arrhythmias including torsade de pointes) will be excluded. Other exclusion criteria include using drugs with potential interaction with Hydroxychloroquine + Lopinavir/Ritonavir, Interferon-β 1a, Interferon-β 1b, pregnant or lactating women, history of alcohol or drug addiction in the past 5 years, blood ALT/AST levels > 5 times the upper limit of normal on laboratory results and refusal to participate.

This study will be undertaken at the Loghman Hakim Hospital, Shahid Beheshti University of Medical Sciences.

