**Intervention and Comparator:**

COVID-19 confirmed patients will be randomly assigned to one of three groups, with 20 patients in each. The first group (Arm 1) will receive Hydroxychloroquine + Lopinavir / Ritonavir (Kaletra) + Interferon-β 1a (Recigen), the second group (Arm 2) will be administered Hydroxychloroquine + Lopinavir / Ritonavir (Kaletra) + Interferon-β 1b (Ziferon), and the control group (Arm 3) will be treated by Hydroxychloroquine + Lopinavir / Ritonavir (Kaletra).

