# **STUDY DESIGN**

**General**

This is a single center, open label, randomized, controlled, parallel group, clinical trial that will be conducted at Loghman Hakim Medical Education Center in conjunction with Shahid Beheshti University of Medical Sciences.

Eligible patients with confirmed SARS-Cov-2 infections will be randomly assigned in a 1:1:1 ratio to one of the three following therapeutic regiments: 1) IFNβ1a (Recigen) (Subcutaneous injections of 44μg (12,000 IU) on days 1, 3, 6) + Hydroxychloroquine + Lopinavir/Ritonavir (Kaletra) [IFNβ1a group], 2) IFNβ1b (Ziferon) (Subcutaneous injections of 0.25mg (8,000,000 IU) on days 1, 3, 6) + Hydroxychloroquine + Lopinavir/Ritonavir (Kaletra) [IFNβ1b group], and 3) Hydroxychloroquine (Single dose of 400 mg on day 1, orally, in all three arms) + Lopinavir/Ritonavir (Kaletra) (400mg/100 mg twice a day for 10 days, orally, in all three arms) [control group]. All three groups will receive standards of care consisting of the necessary oxygen support, non-invasive, or invasive mechanical ventilation.

Patients will be randomly allocated to three therapeutic arms using permuted, block-randomization to balance the number of patients allocated to each group. The permuted block (three or six patients per block) randomization sequence will be generated, using Package ‘randomizeR’ in R software version 3.6.1. and placed in individual sealed and opaque envelopes by the statistician. The investigator will enroll the patients and only then open envelopes to assign patients to the different treatment groups. This method of allocation concealment will result in minimum selection and confounding biases.

The present research is open-label (no masking) of patients and health care professionals who are undertaking outcome assessment of the primary outcome - time to clinical improvement.

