## **Drop Out**

In the event of developing an allergic reaction to the drug or the patient's refusal to cooperate, the participant will be considered as a dropout. Any other reason resulting in discontinuation of the therapeutic regiments would also be considered as a dropout.

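### Hydroxychloroquine, part of every arm, has two incompatible doses: a single 400 mg dose in one section and a 10- to 11-day twice-daily course in another

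*Protocol*

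**What the plan says.** Three places in the Protocol describe how hydroxychloroquine is given.

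- Protocol Summary, Participants: "Although Hydroxychloroquine will be administered in a single dose, patients with heart problems" are to be excluded. This says one dose but gives no milligram amount.
- Study Design, General: "Hydroxychloroquine (Single dose of 400 mg on day 1, orally, in all three arms"). This is the only place that attaches 400 mg to the single dose.
- Study Design, Study Drugs: "400mg bid for first day then 200mg bid for 10 days".

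The drug is part of the comparator. According to Intervention and Comparator, "and the control group (Arm 3) will be treated by Hydroxychloroquine + Lopinavir / Ritonavir (Kaletra").

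Two further statements bear on the point. The Drop Out section says: "Any other reason resulting in discontinuation of the therapeutic regiments would also be considered as a dropout". Lopinavir/ritonavir, the other background drug, is "400mg/100 mg twice a day for 10 days, orally, in all three arms" in the General section and "400mg/100mg bid for 10-14 days" under Study Drugs.

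**The concern.** The two hydroxychloroquine schedules already disagree on day 1, so they cannot be read as a short and a long form of the same instruction. The protocol does not present them as alternatives, link them to a date or a patient subgroup, or say which section takes precedence. All three statements are complete sentences or entries in current text.

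Three things depend on which schedule applies.

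1. **Dosing safety.** The protocol itself connects hydroxychloroquine with cardiac risk, since the summary introduces the QT, PR, heart block and arrhythmia exclusions in the same sentence as the single dose. A reader who looks up the dose under Study Drugs would give the drug for 10 to 11 days alongside lopinavir/ritonavir, instead of on one day.
2. **Comparator.** The primary objective sets interferon against the usual regimen. Hydroxychloroquine is half of that regimen's drug content, so with two doses written the comparator is not uniquely defined and the trial cannot be reproduced from its protocol.
3. **Dropout status.** Stopping the regimen makes a patient a dropout. After a single dose there is no hydroxychloroquine left to stop; under the longer course it can be stopped on any day from day 2 to day 10 or 11.

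**Working it through.** The protocol gives no cumulative dose, so there is no stated total to reproduce. The inputs are the dosing statements in the General and Study Drugs sections.

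**Single dose (General)**

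- Total: 1 × 400 = 400 mg; 1 administration; 1 day.

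**Course (Study Drugs)**

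The wording does not settle whether the 10 days follow day 1 or include it, so both readings are shown.

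- 10 days after day 1: 2 × 400 + 10 × 2 × 200 = 800 + 4,000 = 4,800 mg; 2 + 20 = 22 administrations; 11 days.
- 10 days including day 1: 2 × 400 + 9 × 2 × 200 = 800 + 3,600 = 4,400 mg; 2 + 18 = 20 administrations; 10 days.

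**Comparison**

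| | General | Study Drugs | Ratio |
|---|---|---|---|
| Day 1 dose | 400 mg | 800 mg | 2 |
| Total dose | 400 mg | 4,400 to 4,800 mg | 11 to 12 |
| Administrations | 1 | 20 to 22 | 20 to 22 |
| Days of exposure | 1 | 10 to 11 | 10 to 11 |

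The day 1 row settles compatibility: 400 mg and 800 mg cannot both be right for the same patient.

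**Lopinavir/ritonavir**

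- General: 10 × 2 = 20 administrations.
- Study Drugs: 10 × 2 = 20 to 14 × 2 = 28 administrations.

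These agree at 10 days, so the only gap is that no rule is given for continuing past day 10.

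**Effect on the comparison between arms**

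Hydroxychloroquine is given in all three arms. If one schedule is used throughout, exposure is the same by design in each arm. The stated sample-size inputs (hazard ratio 3.0, alpha 0.05, power 80%, 80% reaching the outcome, 15% dropout) contain no dose term.

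**The case against.** The strongest reply is that this has no consequence for inference. The drug is common to all arms, the interferon contrast stays unbiased under either schedule, and the sample size does not move. That is correct, and no bias between arms is claimed. It does not answer the safety and comparator points.

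Other objections narrow the supporting arguments:

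- **Source of the 400 mg.** The summary says only that the dose is single; the amount rests on the General section alone. This is right, but the summary still contradicts a multi-day course.
- **Cardiac exclusions.** The summary's wording is concessive: patients are excluded even though the dose is single. The Exclusion Criteria section lists essentially the same conditions without reference to dose, and Safety Assessments requires daily monitoring in any case. Nothing in the document shows that the exclusions would be inadequate for the longer course. That stands, so the point is that they should be confirmed against the regimen retained, not that they are deficient.
- **Dropout.** Every arm already has at least 10 days of lopinavir/ritonavir that can be stopped. The extra dropouts under the longer course are therefore only patients who stop hydroxychloroquine alone, or who stop on a possible day 11. This stands, and the dropout effect is small.
- **Timing.** Enrolment was set for 9 to 14 April 2020, yet the Primary Outcome text cites a web page accessed on 15 May 2020 and the Participants section reports assignments in the past tense. This version may post-date dosing. If so, the regimen can no longer be chosen, but the protocol can still state which one was given.

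**Conclusion.** The contradiction is real and the protocol is wrong as written: at least one of the two hydroxychloroquine schedules is incorrect. They differ 2-fold on day 1 and 11- to 12-fold in total (400 mg against 4,400 to 4,800 mg), for all 60 planned patients. The range reflects only the ambiguity over whether the 10 days include day 1.

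This must be corrected because it concerns the dose of a drug given to every patient, for which the protocol itself raises a cardiac concern, and because it leaves the control regimen undefined. The consequences lie in safety, comparator definition and reproducibility. The conclusion that the randomised contrast is unaffected assumes that a single schedule was, or will be, applied in all three arms. The lopinavir/ritonavir mismatch is minor and does not carry the finding.

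**What to change.** State one hydroxychloroquine regimen, identical for all arms, in the summary's Participants paragraph, in the General section and under Study Drugs. The first two agree on a single dose, so the likely correction is to replace the Study Drugs entry with a single 400 mg oral dose on day 1, subject to confirmation by the clinical team.

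If the multi-day course is the intended one, correct the other two sections and say whether the 10 days include day 1. In either case, confirm that the cardiac exclusions in the summary and in Exclusion Criteria suit the regimen retained. If dosing is already complete, record the regimen actually given.

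As a secondary edit, give lopinavir/ritonavir a single duration or a rule for going beyond 10 days.

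The cost is wording changes in up to three places and one clinical confirmation. No patients, visits or data collection are added.

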**Secondary objectives**

The secondary objectives for this study are:

1. To determine and compare the frequency of side effects in three therapeutic arms
2. To determine and compare the average level of oxygen saturation (Sat O2) in three therapeutic arms.
3. To determine and compare the average respiratory rate (RR) in three therapeutic arms
4. To determine and compare the average length of hospital stay in three therapeutic arms
5. To determine and compare the average length of hospital stay in the intensive care unit (ICU) between three therapeutic arms
6. To determine and compare the frequency of 30-days mortality rates between three therapeutic arms
7. To determine and compare the average time to improve clinical symptoms between three therapeutic arms
8. To determine and compare the average SOFA score in three therapeutic arms
9. To determine and compare the average duration of mechanical ventilation use between three therapeutic arms

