## **Exclusion Criteria**

- Refusal to participate expressed by patient or legally authorized representative if they are present
- Patients with prolonged QT or PR intervals, Second or Third Degree heart block, Arrhythmias including torsade de pointes
- Patients using drugs with potential interaction with Hydroxychloroquine + Lopinavir/Ritonavir, Interferon-β 1a، Interferon-β 1b.
- Pregnant or lactating women.
- History of alcohol or drug addiction in the past 5 years.
- Blood ALT/AST levels > 5 times the upper limit of normal on laboratory results.

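### Hydroxychloroquine, given in all three arms, is a single dose in two places and a 10- to 11-day twice-daily course in a third, an 11- to 12-fold difference in total dose

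*Protocol*

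**What the plan says.** Hydroxychloroquine plus lopinavir/ritonavir is the whole drug regimen of the control arm and the background in both interferon arms (Protocol Summary, Intervention and Comparator). Its dosing appears in three places.

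- Study Design, General: "Hydroxychloroquine (Single dose of 400 mg on day 1, orally, in all three arms".
- Protocol Summary, Participants: "Although Hydroxychloroquine will be administered in a single dose, patients with heart problems" are excluded. No amount or day is given.
- Study Drugs: "400mg bid for first day then 200mg bid for 10 days".

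Lopinavir/ritonavir appears in two of these. Study Design, General has "400mg/100 mg twice a day for 10 days, orally, in all three arms", and Study Drugs has "400mg/100mg bid for 10-14 days".

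Three other provisions depend on the background regimen. Exclusion Criteria bars "Patients with prolonged QT or PR intervals, Second or Third Degree heart block, Arrhythmias including torsade de pointes". The first secondary objective is "To determine and compare the frequency of side effects in three therapeutic arms". The Drop Out section, after naming allergy and refusal, adds: "Any other reason resulting in discontinuation of the therapeutic regiments would also be considered as a dropout".

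**The concern.** One dose and a twice-daily course of 10 or 11 days cannot both be followed. All three statements are current text, and none is marked as taking precedence. Four things are at stake.

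1. **Safety.** The Protocol Summary treats hydroxychloroquine as a cardiac concern and offers single dosing as the milder circumstance under which the cardiac exclusions are still kept. Study Drugs removes that premise. The exclusions themselves apply under either schedule.
2. **Side effects.** Their absolute frequency cannot be interpreted without knowing the background dose.
3. **Reproducibility.** A reader cannot tell which usual regimen interferon was added to or compared with.
4. **Dropout.** A patient whose hydroxychloroquine ends after day 1 has completed it under General but stopped early under Study Drugs. If stopping one component counts as discontinuing the regimen, the dropout rule gives opposite answers.

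**Working it through.** Total dose = mg per administration × administrations per day × days. All inputs are the schedules in Study Design, General and in Study Drugs.

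**Hydroxychloroquine**

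- General: 1 × 400 = 400 mg, in 1 administration.
- Study Drugs, with the 10 days following day 1: 2 × 400 + 10 × (2 × 200) = 800 + 4,000 = 4,800 mg, in 2 + 20 = 22 administrations over 11 days.
- Study Drugs, with day 1 counted among the 10 days: 800 + 9 × (2 × 200) = 800 + 3,600 = 4,400 mg, in 2 + 18 = 20 administrations over 10 days.

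| Comparison with General | 11-day reading | 10-day reading |
|---|---|---|
| Ratio of total dose | 4,800 / 400 = 12.0 | 4,400 / 400 = 11.0 |
| Further administrations | 22 − 1 = 21 | 20 − 1 = 19 |

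These ratios are cumulative. The largest single administration is 400 mg in both texts, and the day-1 amount differs 2-fold (800 against 400 mg).

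**Lopinavir/ritonavir (400/100 mg form)**

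- General: 10 × 2 = 20 administrations, or 8,000/2,000 mg.
- Study Drugs: 20 administrations at 10 days, up to 14 × 2 = 28 at 14 days, or 11,200/2,800 mg.
- Upper limit of the difference: 28 − 20 = 8 administrations; 28/20 = 1.4, so 40% more.

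Study Drugs also allows a 5 ml suspension without stating its strength, so these totals hold only for the 400/100 mg form.

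**What is not in conflict.** Interferon beta-1a (44 µg) and interferon beta-1b (0.25 mg), each on days 1, 3 and 6, agree between the two sections. The sample size in Statistical Methods rests on the hazard ratio, event proportion, power, alpha and dropout rate, none of which involves the background dose.

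**The case against.** The strongest reply is that this is a drafting slip in a background drug that leaves the trial's inference untouched. The randomised treatments are specified consistently, both texts give every arm the same background, and the comparison of side effects between arms remains interpretable under any common schedule. That stands: the harm is not to the primary comparison. It does not make the two orders compatible, and a clinician looking up a dose would naturally turn to Study Drugs, the section that disagrees with the other two.

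Four narrower points have some force.

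- The 11- to 12-fold figure is a total, not a per-administration dose, and Safety Assessments requires daily monitoring of adverse effects, vital signs and laboratory tests under either schedule. Both are true, although that section does not name an ECG.
- The dropout conflict depends on reading discontinuation as stopping any one component, and the Drop Out section states no analysis consequence. The conflict is therefore conditional, and no effect on results has been shown.
- A 10-day lopinavir/ritonavir course meets both texts. This part is secondary, but a fixed 10 days is still not a range of 10 to 14 days without a rule, and in an open-label trial that choice falls to unmasked staff.
- An amendment may come too late. Enrolment is given as 9 to 14 April 2020, while the primary-outcome text cites a web page accessed on 15 May 2020. A 14-day course begun on 14 April would end on 27 April. If those dates are right, the text can no longer change what patients received, which makes the record of actual dosing the more useful half of the remedy.

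**Conclusion.** The concern holds. The hydroxychloroquine dosing is wrong as written in at least one section: 400 mg in total against 4,800 mg (12-fold), or 4,400 mg (11-fold) if day 1 is one of the 10 days. The only assumption is how to read those 10 days, and both readings are given. The lopinavir/ritonavir durations also differ, by at most 8 administrations or 40%, and are a lesser matter.

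This must be corrected because it concerns what patients are ordered to take and what the control regimen is. Drug dosing belongs in the protocol, so a statistical analysis plan could not repair it. The interferon comparison remains valid provided one schedule was applied throughout. Uneven dosing between the open-label arms is a possibility only; nothing in the text prescribes it.

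**What to change.** 1. Confirm one hydroxychloroquine schedule, identical in all arms. Two of the three statements point to a single dose, and General puts it at 400 mg on day 1. If the investigators confirm this, replace the hydroxychloroquine line in Study Drugs. If they do not, correct General and remove the single-dose clause from the cardiac sentence in the Protocol Summary.
2. In the same amendment, state one lopinavir/ritonavir duration in General and Study Drugs, or keep 10 to 14 days with a rule, the same in every arm, for going beyond day 10.
3. Apply the Drop Out rule against the confirmed schedule.
4. Check the medication charts. If any patient was treated under the other text, report by arm the hydroxychloroquine and lopinavir/ritonavir actually given.

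The cost is one amendment to the dosing text in three sections and a review of 60 patients' charts. No extra patients or procedures are needed.

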## **Statistical Methods**

Statistical analysis will be performed by R version 3.6.1 software. The total sample size was calculated according to the Latouche and colleagues approach for estimating sample size in survival analysis with 80% power, alpha=0.05, Hazard Ratio (HR) of 3.0 (as the ratio of the hazard rates of time to clinical improvement (TTCI) corresponding to the intervention group compared to the control group) and assuming that 80% of patients would reach the primary outcome (10). The calculations will be carried out using Package ‘powerSurvEpi’ in R and accounted for a dropout

rate of 15%. Overall 60 patients, will be needed for the study, 20 for each arm.

Frequency rates and percentages will be used for categorical variables, and Interquartile Ranges (IQRs) and median will be used for continuous variables. Kruskal-Wallis test will be used for comparing the continuous variables. The Wilcoxon signed-rank test will compare the before and after intervention effects. Moreover, Chi-Square test will compare the frequency of categorical variables. We will use Kaplan–Meier to analyze the TTCI (compared with a log-rank test).

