**Hypothesis**

- The frequency of side effects varies in each of the 3 treatment groups
- The average level of oxygen saturation (Sat O2) varies in each of the 3 treatment groups
- The average respiratory rate (RR) in each of the 3 treatment groups is different
- The average length of hospital stay varies in each of the 3 treatment groups
- The average length of hospital stay in ICU varies in each of the 3 treatment groups
- The frequency of 30-day mortality varies in each of the 3 treatment groups
- The average time until the nasopharyngeal swap test is negative in each of the 3 treatment groups is different
- The average time to clinical improvement in each of the 3 treatment groups is different
- The average SOFA score varies in each of the 3 treatment groups
- The average duration of mechanical ventilation varies in each of 3 treatment groups

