## **Safety Assessments**

Regarding safety concerns, daily monitoring for adverse effects (AEs) and treatment-related AEs, vital signs, and laboratory testing will be carried out. All adverse effects should be recorded and include time, severity, symptoms, and their relation with aforementioned drugs.

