## **Inclusion Criteria**

- Age ≥ 18
- COVID-19 Confirmed Cases by Means of RT-PCR
- Oxygen saturation (SPO2) ≤ 93% OR respiratory rate ≥ 24
- At least one of the following: Calibrated contactless infrared forehead thermometry temperature of ≥37.8, cough, sputum production, nasal discharge, myalgia, headache or fatigue on admission.
- Time of onset of the symptoms should be acute (Days ≤ 14)

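### Respiratory rate is to be compared across arms by an unadjusted Kruskal-Wallis test, although an entry value that could sharpen the comparison is very probably on record

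*Protocol*

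**What the plan says.** Under Study Design, Statistical Methods, the protocol assigns a single between-arm test to all continuous data: "Kruskal-Wallis test will be used for comparing the continuous variables". The only sentence there that uses pre-treatment values is "The Wilcoxon signed-rank test will compare the before and after intervention effects". That is a paired test within patients and does not compare arms. The Protocol Summary mentions an adjusted analysis, but only for the Cox model of time to clinical improvement.

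Respiratory rate is one of the variables to be compared between arms. The third secondary objective reads "To determine and compare the average respiratory rate (RR) in three therapeutic arms", and the Hypothesis section repeats it: "The average respiratory rate (RR) in each of the 3 treatment groups is different". It is not in the list of secondary outcomes, and the protocol does not say at what time it is compared or whether as a final value, a mean or a change.

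Two places point to an entry value. The Inclusion Criteria contain "Oxygen saturation (SPO2) ≤ 93% OR respiratory rate ≥ 24", and Safety Assessments states that "daily monitoring for adverse effects (AEs) and treatment-related AEs, vital signs, and laboratory testing will be carried out".

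**The concern.** A Kruskal-Wallis test on follow-up values leaves in the error term all the variation that a patient's starting rate could explain. With 20 patients per arm, that information is worth having. The eligibility rule admits some patients because they breathe fast and others on oxygen saturation with a rate below 24. The randomisation uses permuted blocks with no stratification factor named, so nothing in the design balances starting rates between arms.

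What is at stake is precision on one secondary objective. An unadjusted comparison has less power than the collected data would probably allow, and its result moves with whatever baseline difference the arms happen to show. The primary outcome and the sample size are not affected.

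**Working it through.** **Inputs from the protocol.** Three arms of 20, allocated 1:1:1; 15% dropout; 80% of patients reaching the primary outcome; and, for the primary outcome only, "80% power, alpha=0.05, Hazard Ratio (HR) of 3.0". Sidedness is not stated, so two-sided alpha is assumed.

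**Inputs that must be assumed.** The protocol gives no standard deviation, effect size, power or baseline-to-follow-up correlation (rho) for respiratory rate. Rho is taken as 0.3, 0.5 and 0.7, and unadjusted power as 80%.

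**1. The protocol's own figure.** Events for a 1:1 pairwise comparison = (1.960 + 0.842)² / (0.25 × (ln 3)²) = 26.01, so 27. Then 27 / 0.80 = 33.75, so 34 patients; 34 / 0.85 = 40 per pair; hence 20 per arm and 60 in all. The stated size reproduces. It concerns time to clinical improvement and implies nothing about power for respiratory rate.

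**2. Detectable difference.** In a two-arm approximation at 20 per arm, 80% power needs a difference of 2.802 × sqrt(2/20) = 0.89 SD.

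**3. Gain from adjustment.** Adjusting for baseline multiplies the residual variance by (1 − rho²), a cut of 9%, 25% and 49% at rho 0.3, 0.5 and 0.7. Adjusted power = Φ(2.802 / sqrt(1 − rho²) − 1.960):

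| rho | sqrt(1 − rho²) | adjusted power | gain over 80% |
|---|---|---|---|
| 0.3 | 0.954 | 83.6% | 3.6 points |
| 0.5 | 0.866 | 89.9% | 9.9 points |
| 0.7 | 0.714 | 97.5% | 17.5 points |

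If unadjusted power is anywhere from 50% to 90%, the gain is 2.5 to 4 points at rho 0.3, 6 to 12 at 0.5 and 9.5 to 28 at 0.7.

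**4. Three-arm simulation.** Normal data, 20 per arm, both interferon arms shifted by the same amount from control. Run A used a 0.9 SD shift, 4,000 repetitions and Quade's test as the rank analysis of covariance. Run B used a 0.92 SD shift, 3,000 repetitions and analysis of covariance on ranks.

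| rho | Run | Kruskal-Wallis, final value | Kruskal-Wallis, change | Rank analysis of covariance |
|---|---|---|---|---|
| 0.3 | A | 80.6% | 64.6% | 84.0% |
| 0.3 | B | 81.9% | 66.6% | 85.0% |
| 0.5 | A | 80.4% | 80.6% | 89.9% |
| 0.5 | B | 82.4% | 82.2% | 91.3% |
| 0.7 | A | 81.1% | 95.4% | 97.2% |
| 0.7 | B | 81.0% | 96.3% | 97.7% |

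Ordinary analysis of covariance in run B gave 86.8%, 93.4% and 98.8%. With no treatment effect, rejection rates were 4.7% to 5.3% in run A and 4.6% to 5.8% in run B, so every method holds its level.

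**5. Chance imbalance.** The baseline difference between two arms of 20 has a standard deviation of sqrt(2/20) = 0.316 baseline SD. The chance that it exceeds 0.5 SD in either direction is 2 × (1 − Φ(0.5 / 0.316)) = 11% for any given pair. At rho 0.5, an imbalance of one such standard deviation moves the unadjusted difference by 0.5 × 0.316 = 0.16 SD.

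**The case against.** The strongest reply is that Kruskal-Wallis is a valid test, the sentence is a general default, and adjustment of an unpowered secondary variable may be set out in an analysis plan that is not at hand. That limits the weight of the point. It does not remove it, because the protocol actively names an unadjusted test for these variables.

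A reader might infer several stronger things that the protocol does not support:

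- **That about 10 points of power are lost.** This holds only near rho 0.5 with 80% unadjusted power, and neither figure is in the protocol. Selecting patients partly on respiratory rate could also lower rho.
- **That the test cannot use the entry value.** It can, if run on change from entry. The form is not stated for respiratory rate, and the neighbouring SpO2 outcome is defined as last minus first measurement. Change scores still fall below rank analysis of covariance at each rho simulated, but by only 1.4 to 1.8 points at 0.7.
- **That chance imbalance biases the result.** Under randomisation it does not; the error rates above already include it. It is the same loss of precision, seen as a dependence on the imbalance observed.
- **That every patient certainly has an entry rate.** The criterion is either/or, so a patient can qualify on SpO2 alone, and no pre-randomisation measurement is explicitly scheduled. Its availability is a reasonable inference.

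The simulations also assume complete, normal data. Dropout, discharge, ventilation and death would leave fewer follow-up values or make them harder to interpret. Finally, Quade's test gives a p-value but no estimate of the difference in average rate that the objective asks about. These last two points stand as limits on the numbers and on the remedy.

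**Conclusion.** The point holds as a modest, low-cost improvement. The protocol fixes an unadjusted rank test for respiratory rate where a baseline-adjusted one would very probably be feasible and more precise. Assuming rho of 0.3 to 0.7 and 80% unadjusted power at 20 per arm, power would rise to about 84% to 97%, with about 90% at rho 0.5 and type I error near 5%. The direction of the gain is the same across these values and whether the sponsor meant final values or change scores; its size depends on the assumptions. The planned analysis is neither invalid nor biased. Because this is a secondary objective without stated power, the priority is low.

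**What to change.** In the protocol's Statistical Methods section, add that respiratory rate at one named follow-up point is compared across the three arms by an analysis of covariance adjusted for the last value before randomisation. The last recorded in-hospital value would match the way SpO2 is already defined under Secondary Outcomes. A rank-based version (Quade's test) keeps the nonparametric approach: rank the entry and follow-up values, regress the second on the first, and compare the residuals across arms. If an estimated difference is wanted as well, ordinary analysis of covariance supplies one. Keep Kruskal-Wallis for continuous outcomes with no baseline value, such as ICU stay or duration of ventilation.

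The sponsor should confirm that a pre-randomisation respiratory rate is recorded for each patient. Beyond that, the cost is a short addition to the text, a few lines of R and one degree of freedom, with no extra patients or visits.
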